## Abstract

**Introduction:**

Perioperative anxiety is a widespread psychological issue among patients undergoing surgery and often has a significant impact on patient outcomes. Due to physiological and psychological characteristics such as hormonal fluctuations and higher emotional sensitivity, female patients generally have a higher incidence of perioperative anxiety compared to male patients. This investigation aims to examine the repetitive transcranial magnetic stimulation (rTMS) effects on perioperative anxiety in female patients.

**Methods:**

This single-center, randomized, regulated investigation will be performed at the Affiliated Hospital of Jiaxing University. The investigation plans to enroll 252 female individuals scheduled for elective surgery under general anesthesia, who will be classified in a random manner to active rTMS or sham rTMS. The primary outcome is the change in anxiety score from baseline to 3 days post-operation. Secondary outcome measures include anxiety scores, occurrence of postoperative delirium (POD), pain scores, frailty scores, and sleep quality scores. Intention-to-treat and per-protocol populations were employed to conduct analyses.

**Discussion:**

This research aims to estimate the influence of rTMS on perioperative anxiety in female patients. It is expected to offer a successful non-pharmacological treatment approach for clinical practice, alleviate anxiety symptoms in female patients during the perioperative period, and enhance the safety of surgical procedure and the quality of post-operative recovery for patients.

**Clinical trial registration:**

https://www.chictr.org.cn/index.html, identifier ChiCTR2500097991.

## Introduction

1

Perioperative anxiety is a prevalent psychological issue among surgical patients, characterized by a diffuse sense of tension and unease stemming from factors such as the underlying disease, hospitalization, anesthesia, and uncertainty about the surgical procedure (1). It encompasses both preoperative and postoperative anxiety (2). The incidence of perioperative anxiety varies across different disease populations, ranging from 11 to 80% (3). Data from the National Institute of Mental Health indicate that females are more susceptible to various anxiety symptoms than males. Further research reveals that the occurrence of anxiety disorders in females is 1.3 to 2.4 times higher than in males, with this disparity being particularly pronounced during the perioperative period, where the incidence significantly exceeds that in males (4, 5). This gender difference involves both biological factors, such as hormonal influences, as well as psychological and sociocultural factors, including gender role expectations and stress coping strategies (6–8). In the surgical setting and under stressful conditions, the occurrence of perioperative anxiety is significantly increased in female patients, with anxiety levels often peaking on the night before or the morning of operation (5, 9). Preoperative anxiety increases both physiological and psychological burden, adversely affecting short- and long-term recovery outcomes. These include heightened postoperative pain, extended hospital stays, and delayed convalescence (10, 11). Moreover, anxiety is closely associated with other psychiatric conditions such as depression, cognitive decline, and sleep disturbances (12, 13). Thus, early intervention for pre-operative anxiety is important.

Pharmacological and non-pharmacological strategies are commonly employed in clinical practice to alleviate perioperative anxiety. Pharmacological interventions mainly include benzodiazepines, non-benzodiazepine anxiolytics, and antidepressants (1). Among benzodiazepines, midazolam is frequently the preferred option due to its short half-life and relatively favorable side effect profile. However, long-term use of benzodiazepines may lead to tolerance or dependence, and these agents have been associated with an increased risk of postoperative cognitive dysfunction and delirium (14). Non-pharmacological approaches encompass preoperative education, music therapy, and cognitive-behavioral techniques (CBT) (15). However, CBT typically requires multiple sessions and may not be feasible in the limited perioperative timeframe. Preoperative education and music therapy is safe and accessible but often yields modest effects (16). Non-invasive central neuromodulation technologies such as tDCS have also shown the potential to relieve perioperative anxiety, but the application of rTMS for perioperative anxiety remains limited (17, 18).

In 1985, Barker et al. (19) introduced transcranial magnetic stimulation (TMS), a non-invasive brain stimulation technique. By placing a coil on the scalp, TMS generates a magnetic field that penetrates the skull and induces electrical currents in the cerebral cortex, resulting in neuronal membrane depolarization, action potential generation, and modulation of cortical excitability in targeted brain regions (20). Repetitive TMS (rTMS), a specific form of TMS, delivers magnetic pulses at regular intervals. It is now widely used in the treatment of various neuropsychiatric disorders, and clinical research on its application in anxiety spectrum disorders continues to expand globally (21). Most studies have focused on its emotional and physiological effects on the dorsolateral prefrontal cortex (DLPFC) (22, 23). However, evidence about the rTMS effects on perioperative anxiety remains inadequate. Therefore, this investigation aims to estimate the impact of rTMS on perioperative anxiety in females and to provide clinical evidence supporting its use as an intervention for anxiety relief in the perioperative setting.

## Methods and analysis

2

### Study design

2.1

This randomized controlled study will be conducted at The Affiliated Hospital of Jiaxing University. Participant recruitment is scheduled to begin on March 2, 2025. A total of 252 female patients undergoing elective surgery will be enrolled and randomly assigned in a 1:1 ratio to either the active rTMS group or the sham rTMS group. Ethical approval for the study was granted by the hospital’s Ethics Committee (Approval No. 2025-KY-049) on February 12, 2025. The trial was registered with the Chinese Clinical Trial Registry on February 14, 2025 (Registration No. ChiCTR2500097991). The schedule for enrollment, interventions, and assessments is presented in Table 1, and study design is illustrated in the flowchart (Figure 1).

**Table 1 tab1:** Study timeline.

Timepoint	Study period					
	On the day pre-operation	on the day of operation	T1	T2	T3	T4
Enrolment						
Inclusion criteria	**×**					
Exclusion criteria	**×**					
Informed consent	**×**					
Randomization	**×**					
Allocation						
Interventions						
Active rTMS group	**×**	**×**				
Sham rTMS group	**×**	**×**				
Outcome measurement						
HADS-A	**×**		**×**	**×**	**×**	**×**
NRS			**×**	**×**	**×**	
POD			**×**	**×**	**×**	
FRAIL			**×**	**×**	**×**	**×**
PSQI			**×**	**×**	**×**	**×**

PSQI, Pittsburgh Sleep Quality Index; NRS, Numeric Rating Scale; POD, postoperative delirium; rTMS, repetitive transcranial magnetic stimulation; FRAIL, Fatigue, Resistance, Ambulation, Illness and Loss of Weight Index; T1, the 1st day post-operation; HADS-A, Hospital Anxiety and Depression Scale-Anxiety subscale; T2, the 2nd day post-operation; T3, the 3rd day post-operation; T4, the 3rd month post-operation.

**Figure 1 fig1:**
[figure not shown]
The flow chart of the study. rTMS, repetitive transcranial magnetic stimulation; ITT, intention-to-treat; PP, per-protocol.

### Eligibility criteria

2.2

#### Inclusion criteria

2.2.1

Females ≥ 18 years oldIndividuals scheduled for operation under general anesthesiaASA grade ≤ IIIHospital Anxiety and Depression Scale-Anxiety (HADS-A) Scale score ≥ 8 pointsCompliant with ethics, individuals voluntarily contribute to the trial and provide informed consent

#### Exclusion criteria

2.2.2

Did not provide informed consentPatient has a history of neuropsychiatric illness or previous neuropsychiatric disorderHistory of craniocerebral or scalp injury or surgeryHave severe cardiovascular and cerebrovascular diseases*In vivo* metal implantsLong-term use of psychotropic substances or abuse of alcohol or illicit drugsPregnant or lactating women

#### Withdrawal or dropout criteria

2.2.3

Participants may leave from the investigation at any time for any reason with no penalty. Continuous care will be ensured, and reasons for withdrawal will be documented. The investigator will discontinue the participation of any subject if any of the following conditions occur during the study:

Failure to strictly follow the study planFailure to complete follow-up visitsInability to tolerate repeated TMS interventionWithdrawal from the study due to personal reasons

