## Randomization and blinding

2.3

This study utilizes a block randomization method. A computer-generated random block sequence of 4 or 6 will be used to centrally randomize participants into either the active rTMS group or the sham rTMS group at a 1:1 ratio. The randomization sequence was generated by an independent researcher from the study team using a computer-based program. This researcher had no involvement in participant recruitment, intervention delivery, outcome assessment, or data analysis. Sequentially numbered, opaque, sealed envelopes were used to ensure allocation concealment. After enrollment and baseline assessment, the envelope was opened by the operator responsible for administering the rTMS at the time of the first rTMS session to determine group assignment. To ensure effective blinding, both groups will use identical stimulation equipment and follow the same operating procedures. However, the device used in the sham rTMS group will not deliver pulsed magnetic fields to the brain; it will only produce sounds and vibrations similar to those generated during actual pulse stimulation. Throughout the study, all other parties, including the participants, outcome assessors, and data analysts, will remain blinded to group assignment.

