## Study interventions

2.5

All rTMS procedures were performed by professionally trained and experienced operators who had undergone standardized training prior to study initiation. The rTMS intervention is administered on the day before surgery and the day of surgery, resulting in two sessions per participant. This protocol is designed to accommodate the limited perioperative time window while providing a rapid, clinically feasible intervention.

Stimulation parameters are based on established neurophysiological principles. The right dorsolateral prefrontal cortex (DLPFC) is selected as the target region due to its role in negative emotional processing and its involvement in anxiety-related neural circuits. Low-frequency (1 Hz) stimulation is applied to reduce cortical excitability and modulate prefrontal–limbic pathways. The entire procedure strictly followed a unified protocol to ensure consistency in coil positioning, stimulation parameters, and patient interaction.

First, a circular coil was used to locate the stimulation target. The primary motor cortex (M1) was clinically identified as the area 2 cm anterior and 1–1.5 cm lateral to the intersection of the naso-occipital line and the temporoparietal line on the patient’s scalp (i.e., the Cz point). The resting motor threshold (RMT) for each patient was then determined as a reference for setting the stimulation intensity, expressed as a percentage of the rTMS device’s maximum output (24). The RMT was defined, using the visual observation technique, as the lowest stimulation intensity capable of eliciting a visible contraction in the target muscle in 5 out of 10 trials while the muscle was completely relaxed (24). Subsequently, a figure-8 coil was used to target the right DLPFC. The center of the coil was positioned parallel to the patient’s scalp, with its midpoint aligned directly over the stimulation site. The rTMS treatment was then delivered at an intensity of 80–120% of the RMT using a low frequency of 1 Hz (21). Both groups will undergo the intervention using identical devices and operational procedures. However, in the sham rTMS group, the device will not deliver pulsed magnetic fields to the brain but will only produce similar audible clicking sounds and scalp sensations/vibrations mimicking those emitted during active stimulation.

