### Primary outcome

2.7.1

The primary outcome is the change in anxiety score from baseline to 3 days post-operation, measured using the HADS-A (25), with a score of ≥8 indicating clinically significant anxiety (26). The minimal clinically important difference (MCID) for the Hospital Anxiety and Depression Scale (HADS) is not fixed and varies across clinical contexts and analytical methods. Evidence from anchor-based studies and systematic reviews suggests that a change of approximately 1.5–2.0 points in the HADS total or subscale scores is generally considered clinically meaningful (27–29). Anxiety was assessed preoperatively in the ward on the day pre-operation (T0) prior to the first rTMS intervention, and the second intervention was administered in the pre-operative holding area on the day of operation. Postoperative anxiety scores were measured on days 1 (T1), 2 (T2), 3 (T3), and the 3rd month post-operation (T4).

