## Statistical analysis

2.11

All analyses will be conducted according to the intention-to-treat (ITT) principle, with participants assessed in their originally assigned groups regardless of protocol adherence or treatment received. Baseline demographic and clinical characteristics will be summarized to evaluate balance between the groups. Continuous variables will be assessed for normality using the Shapiro–Wilk test. Normally distributed variables will be presented as mean ± standard deviation (SD) and compared using independent t-tests, while non-normally distributed variables will be expressed as median (interquartile range, IQR) and analyzed using the Mann–Whitney U test. Categorical variables will be expressed as counts and percentages and compared using the chi-square test or Fisher’s exact test.

The primary outcome will be analyzed using a linear mixed-effects model, including treatment group, time, and treatment-by-time interaction as fixed effects, and a random intercept for each subject to account for within-subject correlations. Baseline HADS-A score, age, type of surgery, and relevant perioperative variables (e.g., anesthesia duration) will be included as covariates to control for potential confounding.

Secondary outcomes will be assessed via a linear mixed-effects model, comprising baseline values as covariates. Fixed effects will involve treatment, time, and the treatment-by-time interaction, with a random intercept for subjects accounting for within-subject variability. The treatment-by-time interaction will be initially examined. If significant, group differences and within-group changes at each time point will be assessed, with Bonferroni correction applied for multiple comparisons of baseline changes in anxiety scores. If not significant, only the major effect of treatment will be evaluated, and no Bonferroni correction will be utilized for time-specific treatment effects. Binary outcomes will be compared via the *χ*^2^ test or Fisher’s exact test, with relative risk (RR) and 95% confidence intervals (CI) reported.

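### Section 2.2.3 ends study participation for deviation, incomplete follow-up or TMS intolerance without separating this from stopping stimulation, which undercuts the intention-to-treat analysis promised in 2.11

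*Protocol article*

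**What the plan says.** Section 2.2.3 (Withdrawal or dropout criteria) is worded as an obligation: "The investigator will discontinue the participation of any subject if any of the following conditions occur during the study". Four conditions follow: not adhering strictly to the plan, not completing follow-up, not tolerating the stimulation, and leaving for personal reasons. For those who leave, the section says "Continuous care will be ensured, and reasons for withdrawal will be documented". It says nothing about further outcome assessment.

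Section 2.11 (Statistical analysis) commits every analysis to intention-to-treat and spells out what that means for the groups compared: "with participants assessed in their originally assigned groups regardless of protocol adherence or treatment received". The abstract adds a second population: "Intention-to-treat and per-protocol populations were employed to conduct analyses".

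On timing, section 2.5 says "The rTMS intervention is administered on the day before surgery and the day of surgery, resulting in two sessions per participant". Section 2.7.1 says "The primary outcome is the change in anxiety score from baseline to 3 days post-operation, measured using the HADS-A", with postoperative scores on days 1, 2 and 3 and at month 3 (T1 to T4).

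Section 2.12 uses complete-case analysis if loss to follow-up is below 10%, and multiple imputation by chained equations under a missing-at-random assumption if it is 10% or more.

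**The concern.** An intention-to-treat analysis needs outcomes from participants who deviated or did not get the full intervention. Section 2.2.3 takes those same participants out of the study because they deviated. If HADS-A is not collected after that, the set with day-3 data drifts towards a per-protocol set under an intention-to-treat label.

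The loss may also be selective. Intolerance of stimulation can depend on the arm, because "the device used in the sham rTMS group will not deliver pulsed magnetic fields to the brain". The operator opens the allocation envelope (2.3) and so knows the arm, and is well placed to observe intolerance or deviation. The condition on strict adherence has no threshold, which leaves room for judgement. A day-3 score that was not collected cannot be recovered later by any analysis plan.

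**Working it through.** **1. Does participation mean the study or only the stimulation?** Both sessions are over by the day of surgery, and T1 is the day after. No stimulation remains to be stopped when a follow-up visit is missed, so that condition can only mean leaving the study. The section heading points the same way.

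**2. What data remain after removal?** Scores already collected stay available, and the mixed model in 2.11 can use them. Someone removed at either session has only the T0 score. Someone removed between T1 and T3 has some postoperative scores but no day-3 score.

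**3. The plan's own sample size (2.10).** Inputs: difference 1.3, SD 2.9, alpha 0.05 (two-sided assumed), power 0.80.

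n per group = 2 × (1.960 + 0.842)² × 2.9² / 1.3² ≈ 78.1, which is 79 rounded up. The stated 78 reproduces to within rounding. Allowing 10% dropout, 78 / 0.90 = 86.7, so 87. The remainder up to 126 is attributed to subgroup analyses.

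**4. Is power the problem?** No. Power for 1.3 points with 126 per group recruited:

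| Loss in each arm | Left per group | Power |
|---|---|---|
| 0% | 126 | 94.5% |
| 10% | 113 | 92.1% |
| 20% | 100 | 88.7% |
| 38% | 78 | 79.9% |

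**5. Selection bias in a completers-only comparison.** Let r be the removal rate in an arm, and D the number of points by which removed participants would have scored worse than retained ones, taken as equal in both arms. The full-arm mean is the retained mean + r × D, so the retained mean is too low by r × D. The benefit of active rTMS is therefore overstated by

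(r active − r sham) × D.

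Neither r nor D is in the article, so every row below is an assumption:

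| Active vs sham removed | Overall | Shift for D = 1 to 3 | Share of 1.3 | Route under 2.12 |
|---|---|---|---|---|
| 10% vs 5% | 7.5% | 0.05 to 0.15 | 4% to 12% | complete case |
| 10% vs 2% | 6% | 0.08 to 0.24 | 6% to 18% | complete case |
| 14% vs 5% | 9.5% | 0.09 to 0.27 | 7% to 21% | complete case |
| 20% vs 5% | 12.5% | 0.15 to 0.45 | 12% to 35% | imputation |
| 30% vs 10% | 20% | 0.20 to 0.60 | 15% to 46% | imputation |

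The formula describes the planned handling only in the first three rows. In the last two, 2.12 calls for imputation, and the figures show what a completers-only analysis would give. For anyone removed before T1, imputation has no postoperative score of her own to work from, so it corrects the shift only as far as baseline data explain it.

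**The case against.** The strongest reply is that the two sections answer different questions: 2.11 says in which arm people are analysed, 2.2.3 says who leaves. Incomplete follow-up weakens an intention-to-treat analysis without making it impossible, and the article supplies a mixed model, imputation and a review of missingness. The list can also be read as categories of dropout, since leaving for personal reasons is not something an investigator imposes. Naming a per-protocol population makes little sense if every deviator is removed, so loose wording is a fair explanation. The article is condensed, and the flow chart is not available here.

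Much of this stands, and it limits the point. Four stronger readings are tempting but unsupported:

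- **That the outcome data will not exist.** This is true only of scores after removal.
- **That one missed T1 visit removes a participant before day 3.** This is the strictest reading; the condition may mean loss to follow-up.
- **That loss will be larger in the active arm and favour rTMS.** No tolerability rates by arm are given, and sham imitates the sound and scalp sensation. Deviations and missed visits have no stated link to arm, and the direction also needs removed participants to score worse.
- **That a large imbalance passes straight into the estimate.** At 20% versus 2%, for example, overall loss is 11%, which triggers imputation, so the completers-only formula does not describe the planned analysis.

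Size also needs perspective. A shift of 0.16 points (10% versus 2%, D = 2) is under half the standard error of the planned comparison, 2.9 × √(2/126) = 0.37.

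What does not stand is treating the matter as detail left to another document. The article itself states a mandatory removal rule, and no analysis plan can supply scores that the protocol stops collecting.

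**Conclusion.** The point holds as a conflict between 2.2.3 and 2.11 as written. The removal rule covers adherence, follow-up and tolerance, it is not confined to stimulation, and the article provides for no outcome collection afterwards. That conclusion needs no assumption about rates.

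The size is conditional. Under assumed differences of 5 to 20 percentage points and gaps of 1 to 3 points, a completers-only estimate shifts by about 0.05 to 0.60 points against 1.3. In the examples that fall under the complete-case rule, the shift is 0.05 to 0.27. If removal is balanced between arms and D is equal, this shift is zero. Power is not at risk, but recruiting 252 does not shrink a selection bias.

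**What to change.** Reconcile 2.2.3 with 2.11:

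- Separate discontinuation of stimulation from withdrawal from the study.
- State that every randomised participant continues to be assessed at T1 to T4, including anyone who deviates, stops or misses a session, or misses a visit, unless she withdraws consent.
- Use non-adherence and incomplete follow-up only to define the per-protocol set named in the abstract.

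The decision on when stimulation stops is left as it is.

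The cost is a wording amendment and the continuation of visits already scheduled. Because recruitment was planned from 2 March 2025 under an existing ethics approval, the amendment may need to be notified to the ethics committee.

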## Randomization and blinding

2.3

This study utilizes a block randomization method. A computer-generated random block sequence of 4 or 6 will be used to centrally randomize participants into either the active rTMS group or the sham rTMS group at a 1:1 ratio. The randomization sequence was generated by an independent researcher from the study team using a computer-based program. This researcher had no involvement in participant recruitment, intervention delivery, outcome assessment, or data analysis. Sequentially numbered, opaque, sealed envelopes were used to ensure allocation concealment. After enrollment and baseline assessment, the envelope was opened by the operator responsible for administering the rTMS at the time of the first rTMS session to determine group assignment. To ensure effective blinding, both groups will use identical stimulation equipment and follow the same operating procedures. However, the device used in the sham rTMS group will not deliver pulsed magnetic fields to the brain; it will only produce sounds and vibrations similar to those generated during actual pulse stimulation. Throughout the study, all other parties, including the participants, outcome assessors, and data analysts, will remain blinded to group assignment.

